- 1. Visits and telephone contacts
- Visit 1 (Screening, week -2): Patient information, informed consent and eligibility. OGTT.
- Telephone 1 (week -1): Eligibility.
- Visit 2 (Randomization, week 0): Hyperglycemic clamp. First dose of study treatment.
- Telephone 2 (week 1). Compliance. Second dose of study treatment.
- Telephone 3 (week 2). Compliance. Third dose of study treatment.
- Telephone 4 (week 3). Compliance. Fourth dose of study treatment.
- Visit 3 (week 4). Safety and fifth dose of study treatment.
- Telephone 5 (week 5). Compliance. Sixth dose of study treatment.
- Telephone 6 (week 6). Compliance. Seventh dose of study treatment.
- Telephone 7 (week 7). Compliance. Eighth dose of study treatment.
- Visit 4 (week 8+0d and week 8+1d). End-of-study investigations (OGTT + hyperglycemic clamp).
- Telephone 8 (week 9). Follow-up safety.
  1. Assessments and Procedures
     1. Recruitment of subjects

Subjects are recruited from the database of the SDPP. Subjects who at follow-up were categorized as having IFG, IGT or IFG + IGT (N=366) at the follow up performed in the years 2003 - 2006 will be contacted for the present study. The screening period will start in Q3 2011. An OGTT will be performed at screening and subjects still having one of the three pre-diabetic conditions, or diet treated diabetes type 2 will be eligible for the study.

1. Selection and Withdrawal of Subjects

The sample size estimation (see section 12.3) requires that 38 subjects should complete the study to investigate the primary endpoint. To compensate for study drop-out, a total of 44 male or female subjects will be included in the study. With a screening failure rate of 30 %, about 58 subjects need to be screened.

- 1. Inclusion Criteria

1. Informed consent obtained before any trial-related activities[[1]](#footnote-2).
2. Meeting criteria for IFG, IGT, IFG+IGT or diabetes mellitus at the screening OGTT.
   - IFG = fasting p-glucose 6.1-6.9 mmol/l
   - IGT = 2 hour p-glucose 7.8-11.0 mmol/l
   - Diabetes = fasting p-glucose ≥ 7.0 mmol/l and/or 2 hour p-glucose ≥ 11.1 mmol/l
3. Age  45 and  75 years, female or male.
4. BMI ≤ 32 kg/m2.
5. HbA1c  ≤ 7.0 % (MonoS) or ≤ 63 mmol/mol (IFCC).
6. Fasting plasma glucose < 9 mmol/l.
7. S-25-OH-vitamin D3 < 75 nmol/l.
8. Able and willing to perform tests and examinations specified in the protocol.
   1. Exclusion Criteria
9. Previous participation in this trial. Participation is defined as randomization.

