The randomization will take place at visit 2 (randomization visit) just prior to initiation of trial treatment. Randomization will be carried out in a 1:1 manner and administered by the Investigator. The treatment assignment will be double-blind. A randomization list will be prepared by a statistician not involved in the study. The list will contain randomization numbers 1 to 44 and corresponding study medication (active substance or placebo) The study medication will be marked with a randomization number, 1 to 44, by APL according to the randomization list. Subjects that are included in the study will sequentially be assigned a randomization number, and thereby the corresponding study medication. Unblinding can be carried out in medical emergencies by the Investigator. Individual treatment codes will be available to the Investigator by personnel at the department not involved in the study. A list with the treatment codes will be kept at Enheten för Metabol kontroll, Endokrinliniken D1:03, Karolinska Universitetssjukhuset Solna, [contact] [name].

- 1. Concomitant Medication

Details of all concomitant medication must be recorded at the screening visit. This should include the start date of medication, and name Subjects will record any changes in concomitant medication in the diary and the investigator will transcribe the information into the CRF at all visits.

- 1. Compliance to Treatment

The IMP will be given by a study nurse at visits to the study site at study weeks 0 and 4. The subjects will take IMP at home at weeks 1,2,3,5,6 and 7. Telephone contacts will be carried out at these time points to optimize compliance. If study subject prefer SMS reminder, this could be done instead of a phone call. The SMS should be confirmed by the patient. Subjects will bring all IMP bottles to the study site for compliance assessment at visit 3 and 4. Serum 25-OH-vitamin D will also be analyzed at week 4 and 8.

- 1. Continuation of Treatment

There will be no active post-treatment follow-up period. At the last visit the subjects will receive information and counseling regarding treatment of their glycemic disturbance. Information will be sent to the subjects´ physicians.

1. Assessments and procedures
   1. Efficacy Assessments

All efficacy assessments will be carried out before and at the end of the intervention period if not stated otherwise.

- - 1. Hyperglycemic clamp

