       The plasma insulin response (I) during hyperglycemic clamp will assess beta cell function [44]. Glucose infusion is administered at a variable rate to increase the plasma glucose to a target value 6.9 mmol/l above the fasting glucose value. Blood samples for glucose and insulin are taken every 2 minutes from minute 0 to 14 and every 5-10 minutes from minute 10 to 120. The ratio of the glucose infusion rate and plasma insulin concentration (M/I) will assess insulin sensitivity. Further, extra archive serum samples will be collected at 0, 10, 60 and 120 minutes.
    2. Oral glucose tolerance test (OGTT)

A sample for fasting plasma glucose and serum insulin will be obtained (0 minutes). 75g of glucose in water will then be given orally. Plasma glucose and serum insulin will be obtained at 30 and 120 minutes after the glucose administration. Glucose will be analyzed in local laboratory by a glucose oxidase method. Further, extra archive serum samples will be collected at 0, 30 and 120 minutes.

- - 1. HbA1c

HbA1c will be analyzed using the high-performance liquid chromatography Mono-S method at Karolinska central laboratory.

- - 1. CVD riskmarkers and Lipids

Serum triglycerides, total cholesterol, HDL, Apo B and Apo A1 will be obtained in fasting state and analyzed at Karolinska central laboratory.

- - 1. Hormones

Serum GLP-1, adiponectin and leptin will be obtained in fasting state and analyzed in local laboratory.

- - 1. 25-OH-vitamin D and PTH

Analyses will be performed at Karolinska central laboratory . 25-OH-vitamin D will also be assessed at week 4 (visit 3).

- - 1. Body composition

Weight, length, BMI and bioimpedance (by Tanita-Body Composition Analyzer).

- - 1. Archive samples

Fasting plasma samples and end-clamp samples for future research will be obtained and frozen at visit 2 and 4.

- 1. Safety Assessments

Adverse events will be recorded at every visit/contact, except for the screening visit. All other safety assessments will be carried out before and at the end of the intervention period if not stated otherwise.

- - 1. Physical Examination

A general physical examination will be carried out at screening and at study end, including: cardiovascular system, respiratory system, gastrointestinal system, central and peripheral nervous system, musculoskeletal system and skin, according to common procedure. Any clinically significant deterioration since the screening visit should be regarded as an adverse event.

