All events meeting the definition of an adverse event must be collected and reported from the first trial related activity after the subject has signed the informed consent and received the first dose of IMP, and until the end of the study. At each contact with the site (visit or telephone), the subject must be asked about adverse events. All adverse events, either observed by the Investigator or reported by the subject, must be recorded by the Investigator and evaluated.

The subject will be asked about adverse events, with a question: “Have you experienced any problems since the last contact? (Swedish: Har du upplevt några besvär sedan vår senaste kontakt?)”

The Investigator should record the diagnosis, if available. If no diagnosis is available the Investigator should record each sign and symptom as individual adverse events.

All adverse events must be recorded by the Investigator on the standard Adverse Event Form. If more than one sign or symptom is to be reported, use a separate Adverse Event Form for each sign and symptom. For serious adverse events, the Serious Adverse Event Supplementary pages must also be completed.

- 1. Reporting of Adverse Events
     1. Reporting of Adverse Events

All AEs will be recorded on a separate AE form in the CRF.

- - 1. Reporting of Serious Adverse Events

In addition will SAEs also be reported by the investigator to the sponsor on a separate SAE form within 24 hours after the SAE have been communicated to the investigator. Follow-up information describing the outcome of the SAE and action taken will be reported as soon as it is available. The original SAE form must be filed with the CRF. The sponsor shall report all cases of death to the MPA within 7 days, and if necessary complete the report to the MPA within 8 days and all cases of death to the Independent Ethics Committee (IEC).

- - 1. Reporting of Suspected Unexpected Serious Adverse reactions

The sponsor must report all SUSARs that resulted in death or was life threatening to the authority through the EudraVigilance database and to the IEC within 7 days, and if necessary complete the report within the following 8 days. Other SUSAR should be reported within 15 days. A CIOMS form will be sent to the MPA, which in turn will report to the EudraVigilance database.

- 1. Follow-up of Adverse Events

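### Section 9.5 lets a confirmed reminder SMS replace six of the nine post-dose contacts at which sections 10.2 and 11.3 require adverse events to be asked about or recorded

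*Protocol*

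**What the plan says.** Section 9.5 (Compliance to Treatment) sets the home doses: "The subjects will take IMP at home at weeks 1,2,3,5,6 and 7". It then gives the reason for the calls in those weeks: "Telephone contacts will be carried out at these time points to optimize compliance". Next comes the substitution, "If study subject prefer SMS reminder, this could be done instead of a phone call", with one condition: "The SMS should be confirmed by the patient". Nothing further is said about the content of the SMS.

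Two other sections give the same calls a second job. Section 10.2 (Safety Assessments) states: "Adverse events will be recorded at every visit/contact, except for the screening visit". Section 11.3 (Methods for Eliciting Adverse Events) states: "At each contact with the site (visit or telephone), the subject must be asked about adverse events". It also scripts the question, which looks back over a variable interval: "Have you experienced any problems since the last contact".

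The list of visits and telephone contacts in the Design section labels the calls at these six weeks as compliance calls. It labels Visit 3 and the last call as safety contacts.

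**The concern.** The calls at weeks 1, 2, 3, 5, 6 and 7 both remind the subject of the dose and carry the adverse event question. Section 9.5 treats them as reminders only and lets a text message stand in for them. A message that is merely confirmed serves the first purpose and not the second. A site that follows section 9.5 as written therefore omits enquiries that section 11.3 makes mandatory.

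Adverse event incidence, intensity, severity and causality are a stated safety endpoint (section 6, Safety Endpoints), in a trial with 22 subjects randomised per arm. How often a subject is asked would depend on a personal preference for texts or calls. Mild, short-lived complaints are the ones most easily forgotten over a longer interval. Onset dates also become less exact, and the analysis of safety endpoints uses dates: an event counts as an adverse reaction only if it falls between the first dose and 7 days after the last.

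**Working it through.** The protocol gives no count of its own to reproduce, so the check is a direct count from the schedule.

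**Inputs**
- Start of the post-dose period: "Visit 2 (Randomization, week 0): Hyperglycemic clamp. First dose of study treatment" (Design, Visits and telephone contacts).
- Scheduled contacts after that visit (same list): Telephone 2, 3 and 4 (weeks 1, 2, 3), Visit 3 (week 4), Telephone 5, 6 and 7 (weeks 5, 6, 7), Visit 4 (week 8, two days counted as one visit) and Telephone 8 (week 9).
- Contacts that an SMS may replace (section 9.5): weeks 1, 2, 3, 5, 6 and 7.

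**Enquiries per subject**
- All calls made: 6 + 2 + 1 = 9 enquiries.
- SMS at every home dose, with no question in the SMS: 9 − 6 = 3 enquiries, at weeks 4, 8 and 9.
- Share dropped: 6/9 = 67%.
- Within the adverse reaction window (last dose at week 7, plus 7 days, so up to week 8), Telephone 8 falls outside. The share dropped is then 6/8 = 75%.

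**Length of recall**
- All calls made: enquiries one week apart, so a look-back of about 1 week each time.
- SMS throughout: enquiries at weeks 4, 8 and 9 after a start at week 0, so look-backs of 4 − 0 = 4, 8 − 4 = 4 and 9 − 8 = 1 weeks.

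**Across the trial**

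The protocol does not say how many subjects would choose SMS. Assume a share p uses it for all six home doses. The share of planned enquiries dropped is then p × 6/9:
- p = 25%: 17%
- p = 50%: 33%
- p = 75%: 50%

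These figures count occasions of asking, not adverse events. The documents give no basis for turning them into a number of missed events.

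**The case against.** **The calls are compliance calls.** Both the contact list and section 9.5 describe them that way. This explains how the conflict arose but does not remove it, because section 11.3 names telephone contacts and uses mandatory wording.

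**The site could add the question to the SMS.** It could, and the text does not forbid it. That is why the count is put as up to 6 of 9. But the protocol does not require it. The visit schedule in Appendix B is not visible in the text at hand and may list adverse event enquiry by contact.

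**Some protection remains.** Section 11.3 also records events that subjects report themselves, the diary of medication changes may jog the memory, and the closing physical examination picks up clinically significant deterioration. These soften the effect but do not replace the scripted question.

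Three stronger readings are tempting, and the documents do not support them.
- *A reader might infer that whole weeks are never asked about.* That requires the SMS to count as a contact for the look-back but not for the duty to ask. Section 11.3 uses the same term for both. If the SMS is a contact, sections 10.2 and 11.3 already call for events to be asked about and recorded. If it is not, the question at Visit 3 reaches back to Visit 2 and the question at Visit 4 back to Visit 3. The protocol should nevertheless close off the mixed reading, since it does not define how an SMS counts.
- *A reader might infer a biased comparison of arms.* The choice of SMS is the subject's own, under double-blind 1:1 allocation, and nothing suggests that it differs by arm. The unevenness is between SMS and telephone subjects.
- *A reader might infer that hypercalcaemia would be missed.* It is defined by a laboratory value, and free calcium is measured at weeks 4 and 8 however the subject is reminded.

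**Conclusion.** The inconsistency is real and modest in size. Followed as written, section 9.5 drops up to 6 of 9 post-dose adverse event enquiries for a subject who uses SMS throughout, and lengthens recall from about 1 week to about 4. Coverage of the period is kept at weeks 4, 8 and 9, so the consequence is less complete and uneven ascertainment, not a demonstrated loss of events. This rests on two assumptions: that the SMS carries no adverse event question, since none is specified, and that the subject uses it at all six home doses. The share of such subjects is unknown. The matter belongs in the protocol because analysis cannot recover complaints that were not elicited. It should be corrected, as the remedy costs almost nothing.

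**What to change.** Reconcile section 9.5 with sections 10.2 and 11.3:
- In section 9.5, state that an SMS replaces the dose reminder only, not the adverse event enquiry.
- Put the section 11.3 question into the SMS with a required yes/no reply, and have the site call back whenever the answer is yes. Alternatively, keep the telephone call for the enquiry.
- In section 11.3, state that an SMS without the question is not the last contact for the look-back at the next visit.

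Leave the scripted question itself unchanged. Asking every subject at Visits 3 and 4 about the time since the previous visit would lead telephone subjects to repeat events already recorded, and so invite duplicates.

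The cost is a few sentences of protocol text, one line in the SMS and a few call-backs. No visits or samples are added.

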1. Occurrence of hypercalcemia during the study, defined as free s-calcium > 1.35 mmol/l. In case of hypercalcemia, a second test should be performed a soon as possible to verify the diagnosis.
2. Initiation of concomitant medication known to interfere with glucose metabolism, such as systemic corticosteroids, non-selective beta-blockers, mono amine oxidase (MAO) inhibitors and anabolic steroids.
3. Initiation of any anti-diabetic medication.
4. Initiation of treatment with phenytoin, barbiturates, rifampicin, isoniazid, cardiac glycosides, orlistat or colestyramin.
5. Pregnancy or intention to become pregnant in female subjects.
   1. Subject Log

All screened subjects will be documented. For subjects who either fail screening or are withdrawn prior to randomization, a Screening Failure Form must be completed including the reason for screening failure.

1. Treatment
   1. Description of Investigational Medicinal Products
      1. Vitamin D3 (Cholecalciferol), Vigantol® Oil

Vitamin D3 will be supplied to the study site in bottles of 10 ml (200 000 IE). Vitamin D3 will be provided by Renapharma AB.

**Dosage form**: Mixture. 20 000 IU/ml (0.5 mg/ml)

**Administration**: Oral.

**Dose**: 30000 IU (1.5 ml) once weekly (corresponding to 4286 IU daily) for 8 weeks.

**Manufacturer**: Merck KGaA

- - 1. Placebo

Matching placebo (oil) will be supplied to the study site in bottles of 10 ml. Placebo will be provided by Renapharma AB.

**Dosage form**: Mixture.

**Administration**: Oral.

**Dose**: 1.5 ml once weekly, for 8 weeks.

**Manufacturer**: Merck KGaA

- 1. Packaging, Labeling, Storage and Handling of Investigational Medicinal Products

The IMP will be supplied to the Karolinska pharmacy who will conduct, in co-operation with Apotek Produktion & Laboratorier AB (APL), the labeling and storage. The IMP will be provided to the study site at study start when all approvals have been granted. The labeling will contain information on the name of the study, protocol number, EudraCT-number, dosing, IMP information (name, strength, form, route of administration and amount), batch number, randomization number and initials, keeping instruction and expiration date, warning text that keep away from children, primary investigator, sponsor and the text “För klinisk prövning”. Also see amendment C.

- 1. Treatment Assignment

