During and following a subject’s participation in the trial, the Investigator should ensure that adequate medical care is provided to the subject for any adverse events, including clinically significant laboratory values related to the trial. The Investigator should inform the subject when medical care is needed for adverse event(s) of which the Investigator becomes aware.

The follow up information should only include new (updated and/or additional) information that reflects the situation at the time of the investigator’s signature.

All AEs, SAEs and SUSARS will be followed until they are classified as “recovered” or “stable” and/or in the care of medical expertise.

1. Statistics and Data Management
   1. Data Management

The subjects and the biological material obtained from the subject will be identified by initials, screening/randomization number, trial site, and trial identification number. Appropriate measures such as encryption or deletion will be enforced to protect the identity of human subjects in all presentations and publications as required by local/regional/national requirements.

Data from CRFs and other source documents will be transferred manually to a database by [name]. A subset of the transferred data will be controlled against source data for verification. Initials and randomization number will be used for identification in the database.

- 1. Statistical Analysis

The Intention-To-Treat (ITT) population will be included in the safety analysis. The ITT population will consist of all randomized subjects who receive at least one dose of IMP. An analysis based on the Per-Protocol (PP) population will be performed on the efficacy variables. The PP population will consist of subjects exposed to trial drug who did not significantly violate the inclusion/exclusion criteria or other aspects of the protocol considered to potentially affect the primary endpoint. Data from drop-outs, withdrawals and non-compliant subjects will hence not be included in the PP analysis.

It is the joint responsibility of the Principal Investigator and the Scientific Advisors to decide on exclusion of observations or subjects from the analysis.

The subjects or observations to be excluded, and the reasons for their exclusion must be documented and signed by the above mentioned persons prior to closing the database. The documentation must be stored together with the remaining trial documentation.

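### Section 12.2 names the per-protocol set for efficacy and states no efficacy analysis by randomised group, so exclusions after randomisation can bias the primary comparison in either direction

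*Protocol*

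**What the plan says.** Section 12.2 (Statistical Analysis) assigns one population to each purpose. For safety: "The Intention-To-Treat (ITT) population will be included in the safety analysis". That set is defined as follows: "The ITT population will consist of all randomized subjects who receive at least one dose of IMP". For efficacy: "An analysis based on the Per-Protocol (PP) population will be performed on the efficacy variables". The consequence is spelled out: "Data from drop-outs, withdrawals and non-compliant subjects will hence not be included in the PP analysis".

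The subsection on efficacy endpoints specifies a Mann-Whitney U test on the change from baseline, two-sided at 5%, and names no other population.

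Exclusions involve judgement: "It is the joint responsibility of the Principal Investigator and the Scientific Advisors to decide on exclusion of observations or subjects from the analysis". The list of exclusions and reasons "must be documented and signed by the above mentioned persons prior to closing the database".

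Section 8.3 (Criteria for Withdrawal) lists events after which a subject must be withdrawn. Two matter here: "Occurrence of hypercalcemia during the study, defined as free s-calcium > 1.35 mmol/l" and "Initiation of any anti-diabetic medication". The investigator may also withdraw a subject for non-compliance or a safety concern.

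**The concern.** The trial is a randomised, placebo-controlled test for a difference between arms. Randomisation makes the arms comparable as allocated. Once subjects are removed for what happens later, that holds only if removal is unrelated to the outcome, or is related to it in the same way in both arms.

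The protocol's own rules leave room for neither condition to hold:

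- **Hypercalcaemia** is a safety endpoint of the vitamin D intervention, so withdrawal for it can depend on arm.
- **Starting anti-diabetic medication** suggests worsening glycaemia, so it is plausibly linked to the beta-cell outcome.
- **Non-compliance** is judged. The compliance section includes serum 25-OH-vitamin D at weeks 4 and 8. If those values were used to judge compliance, they could show missed doses in the vitamin D arm but not in the placebo arm. The protocol does not say whether they will be used in this way.

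At stake are the type I error and the estimated effect of the primary test. With 19 subjects planned per arm, a few exclusions carry weight.

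**Working it through.** **1. Which population goes with which analysis.** Safety has ITT (randomised and at least one dose). Efficacy variables have per-protocol. The primary Mann-Whitney test has no separate designation, so the efficacy assignment applies to it. The sample-size section is consistent with analysing completers: 19 per arm in the final analysis out of 22 randomised.

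**2. The plan's own numbers.** 18 × 1.05 = 18.9, rounded up to 19 per arm, or 38 in total. With 22 per arm randomised (44 in total), the implied loss is 1 − 38/44 = 6/44 = 13.6%. The chain reproduces. No drop-out rate is stated, so 13.6% is back-calculated. The starting figure of 18 rests on precedent, with no SD, effect or power, and cannot be recomputed.

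**3. Illustration with exclusions in one arm.** The documents give no exclusion rates by arm and no link to outcome, so the following are assumptions. The true effect is zero and the SD of change is 1. One arm loses k of 22 and the other loses none. The excluded subjects' mean change lies δ SD below that of the subjects who remain in their arm.

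- Bias = (k/22) × δ
- SE = √(1/(22 − k) + 1/22)
- Type I error = P(|Z + bias/SE| > 1.96), a normal approximation

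| k | δ | Bias (SD) | SE | Bias/SE | Type I error |
|---|---|---|---|---|---|
| 3 | 1 | 0.14 | 0.313 | 0.44 | 7.2% |
| 4 | 1 | 0.18 | 0.318 | 0.57 | 8.8% |
| 5 | 1 | 0.23 | 0.323 | 0.70 | 10.8% |
| 3 | 0.5 | 0.07 | 0.313 | 0.22 | 5.5% |
| 4 | 0.5 | 0.09 | 0.318 | 0.29 | 5.9% |
| 5 | 0.5 | 0.11 | 0.323 | 0.35 | 6.4% |

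The formula does not know which arm is affected. Poor responders removed from the vitamin D arm favour vitamin D; the same removals from the placebo arm count against it.

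**4. Simulation with the Mann-Whitney test.** This used 20,000 replicates, no true effect, 22 per arm and 6 of 44 excluded. In one arm, exclusion had a latent correlation ρ with the outcome; any exclusions in the other arm were random.

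| Excluded (related arm + other arm) | ρ | Bias (SD) | Type I error |
|---|---|---|---|
| 3 + 3 | 0 | about 0 | 4.8% |
| 3 + 3 | 0.3 | 0.08 | 5.2% |
| 3 + 3 | 0.5 | 0.12 | 6.5% |
| 3 + 3 | 1 | 0.24 | 11.4% |
| 6 + 0 | 0 | about 0 | 5.0% |
| 6 + 0 | 0.3 | 0.13 | 6.7% |
| 6 + 0 | 0.5 | 0.22 | 9.8% |
| 6 + 0 | 1 | 0.44 | 29.2% |

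The rows with ρ = 1 are extremes in which exclusion follows the outcome exactly. The rows with ρ = 0 show that exclusions unrelated to outcome cause no bias, even when all fall in one arm.

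**5. Scale.** At 19 per arm, the difference detectable with 80% power is (1.960 + 0.842) × √(2/19) = 0.91 SD, or about 0.93 SD allowing for Mann-Whitney efficiency of 3/π. The biases in step 3 are smaller than this but not negligible beside it.

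**The case against.** The other side has four good arguments.

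**The text does not say that per-protocol is the only efficacy analysis.** It announces an analysis on that set and does not rule out another. A reader might infer that analysis by randomised group is excluded; the words do not go that far. What stands is that ITT is defined and then used for safety alone, and that no efficacy analysis on it is stated.

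**The direction is open.** A reader might infer that the exclusions favour vitamin D. The documents do not support this. If vitamin D works, starting anti-diabetic medication would fall more on placebo, and dropping those subjects would bias against vitamin D. If it does not work, that reason should be balanced between blinded arms. Nothing in the protocol says that subjects with hypercalcaemia would have a poorer insulin response. The risk assessment in section 15.4 also expects little toxicity, so such withdrawals may be few.

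**There are safeguards.** Treatment is double-blind with matching placebo, exclusions are signed before the database closes, and all endpoints are to be reported whatever their significance. These limit selective exclusion. They do not remove bias when withdrawal itself depends on treatment or outcome, and the text does not say that exclusion decisions are made blind.

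**This is a pilot.** A reader might infer that the sample size fails because the 13.6% allowance is described as covering drop-out, while per-protocol also removes non-compliers and violators. Section 12.3 disclaims a formal power calculation, so no stated power is breached. The pilot label does not remove the main point, because a two-sided 5% test is still planned.

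**Conclusion.** The point holds as a defect in the stated choice of population for the primary comparison. It is not a detail left open for a later analysis plan, because section 12.2 makes the assignment.

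The comparison can be biased in either direction. Its size cannot be derived from the documents. Under the assumptions in step 3 of the working (3 to 5 of 22 lost from one arm only, mean change 0.5 to 1 SD below the rest), type I error would be about 5.5% to 11%. At the mild end that is close to nominal, and with exclusions unrelated to outcome there is no bias. These figures illustrate sensitivity and do not predict what will happen.

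**What to change.** **Section 12.2.** State that the primary efficacy analysis includes all randomised subjects who received at least one dose, by assigned arm, using every available Visit 4 clamp regardless of compliance or protocol violation. Keep per-protocol as a supportive analysis, and state that exclusions from it are decided before unblinding. Add a sensitivity analysis for missing Visit 4 values that includes outcome-dependent missingness. Imputation from baseline alone would not be enough, because it assumes that baseline explains the loss.

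**Section 8.3.** Renaming the set recovers only subjects who reach Visit 4. The withdrawal text does not separate stopping treatment from leaving the trial. Reconcile it with section 12.2 so that stopping treatment does not by itself end outcome collection in subjects who still consent. The events that lead to stopping treatment are a clinical matter and are not questioned here.

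**Cost.** Wording in both sections, a few additional Visit 4 assessments of a kind already in the schedule, and slight dilution of any true effect by non-compliers. The number randomised stays at 44. Up to 22 per arm rather than 19 could then enter the primary comparison, if week 8 data are obtained or handled by a stated method.
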